## Abstract

**Background:**

Recently a clinical prediction rule (CPR) has been developed and validated that accurately identifies patients with low back pain (LBP) that are likely to benefit from a lumbo-pelvic thrust manipulation. The studies that developed and validated the rule used the identical manipulation procedure. However, recent evidence suggests that different manual therapy techniques may result similar outcomes. The purpose of this study is to investigate the effectiveness of three different manual therapy techniques in a subgroup of patient with low back pain that satisfy the CPR.

**Methods/Design:**

Consecutive patients with LBP referred to physical therapy clinics in one of four geographical locations who satisfy the CPR will be invited to participate in this randomized clinical trial. Subjects who agree to participate will undergo a standard evaluation and complete a number of patient self-report questionnaires including the Oswestry Disability Index (OSW), which will serve as the primary outcome measure. Following the baseline examination patients will be randomly assigned to receive the lumbopelvic manipulation used in the development of the CPR, an alternative lumbar manipulation technique, or non-thrust lumbar mobilization technique for the first 2 visits. Beginning on visit 3, all 3 groups will receive an identical standard exercise program for 3 visits (visits 3,4,5). Outcomes of interest will be captured by a therapist blind to group assignment at 1 week (3^rd ^visit), 4 weeks (6^th ^visit) and at a 6-month follow-up. The primary aim of the study will be tested with analysis of variance (ANOVA) using the change in OSW score from baseline to 4-weeks (OSW_Baseline _– OSW_4-weeks_) as the dependent variable. The independent variable will be treatment with three levels (lumbo-pelvic manipulation, alternative lumbar manipulation, lumbar mobilization).

**Discussion:**

This trial will be the first to investigate the effectiveness of various manual therapy techniques for patients with LBP who satisfy a CPR.

## Background

An intervention commonly used in the treatment of individuals with low back pain (LBP) is thrust manipulation. The *Guide to Physical Therapist Practice *[1] identifies mobilization/manipulation as an intervention appropriate for the care of patients with spinal disorders. Jette and Jette [2] reported mobilization/manipulation was utilized in 35% of over 1000 patients with LBP treated by physical therapists, less than many other interventions with no supporting evidence. Several randomized trials have found manipulation to be more effective than placebo [3-5] or other interventions [6-9]. However other studies have not shown any benefits for manipulation versus other interventions [10-13]. The disparity in the results of clinical trials may be partly attributable to the admission of all patients with LBP without an attempt to *a priori *identify those likely to benefit from the intervention. A few randomized trials have found manipulation to be more beneficial for a sub-group of patients with more acute symptoms [14,15], or more limited straight leg raise range of motion [16]. Each of these studies was published in 1990 or before, and none sought to develop a multi-factorial classification rule that would maximize the prediction of success with manipulation prior to the intervention.

### Identifying the sub-group of patients likely to respond to spinal manipulation

The classification process can be used to identify patients who will respond favorably to a specific type of treatment based on clusters of signs and symptoms identified during the physical examination. Clinical prediction rules (CPR) are useful to improve the accuracy of the classification of patients. Clinical prediction rules are developed by examining multiple factors from the history and physical examination. Through statistical analysis the most powerful set of predictor variables is identified to maximize accuracy in predicting response to treatment [17].

Recently, a CPR was developed that identifies patients with LBP who are likely to respond with rapid, and prolonged reductions in pain and disability following spinal manipulation (see Additional file 1) [18]. A favorable response to manipulation was defined as a 50% or greater reduction in self-reported disability occurring over two treatment sessions. The CPR developed from this study of 71 patients with non-radicular LBP involved 5 factors; the duration of current symptoms (less than 16 days), score on the work subscale of the Fear-Avoidance Beliefs Questionnaire [19] (less than 19), hypomobility of the lumbar spine, internal rotation of at least one hip greater than 35 degrees, and symptoms not extending distal to the knee. When four out of the five factors were present, the positive LR was 24.4 (95% CI, 4.6 to 139.4). To put this result in perspective, if it is assumed that about 50% of all patients with non-radicular LBP will respond to the manipulation technique, the likelihood of response increases to 97% in an individual with at least four factors present.

A follow-up study [20] was carried out to determine the validity of the CPR developed by Flynn et al [18]. This study randomly assigned 131 patients to receive a standardized exercise program with or without the manipulation technique. Outcomes were assessed at 1 week then at the end of treatment (4 weeks) and at a 6-month follow up. Following data collection a therapist who was blind to treatment allocation determined if the patient satisfied the CPR. The results demonstrated that patients who were positive on the rule and received manipulation experienced greater improvement in 1- and 4-week disability than patients who were negative on the rule and received manipulation. This difference was maintained at the 6-month follow-up. Furthermore, patients who were positive on the rule and received manipulation also experienced greater improvement in 1- and 4-week disability than patients who were positive on the rule but received the exercise. At the 6-month follow-up, patients in the exercise group demonstrated statistically significantly greater medication use, health care utilization, and lost work time due to back pain than patients in the manipulation group. In the manipulation group, positive status on the rule resulted in a positive likelihood ratio of 13.2 (CI, 3.4 to 52.1) for predicting success at 1 week.

#### Generalizability of the manipulation clinical prediction rule

The CPR developed to predict favorable response to manipulation investigated only one manipulation technique, and predominantly used therapists working within the United States Armed Forces. The accuracy of the CPR for predicting the outcomes with therapists in other work settings, or using other manipulation techniques is not known. However, recently, Cleland et al [21] utilized a different manipulation technique than that used in the development of the rule in a consecutive series of patients who satisfied the CPR. Eleven of the 12 patients (92%) in this case series that satisfied the CPR and were treated with an alternative lumbar manipulation technique demonstrated a successful outcome (> 50% reduction in the OSW) in 2 visits. It is plausible that patients with LBP who satisfy the CPR may obtain a successful outcome with different manipulation techniques directed at the lumbopelvic region. However, the inherent limitation of a case series does not allow us to infer a cause and effect relationship between the manipulation and the patient's outcomes. Although some clinicians have argued for superior efficacy with certain techniques recent evidence questions this belief. Chiradejnant et al [22] examined 140 patients with LBP and found no difference in outcomes between patients who received the mobilization technique selected by the treating therapist or a randomly selected technique. Another debate among clinicians is the need to perform thrust manipulation techniques versus non-thrust mobilization techniques. A recent review by Bronfort et al [23] examined the evidence for both thrust manipulation and non-thrust mobilization and concluded that the evidence favors the use of manipulation, particularly for patients with acute LBP, but more studies are needed comparing the different forms of treatment.

The purpose of the present study is therefore to conduct a multi-center randomized clinical trial to compare the outcomes of three different manual therapy techniques in patients with LBP who fit the spinal manipulation CPR. The three techniques used will be; 1) the thrust manipulation technique used in the development of the CPR, 2) an alternative lumbar thrust manipulation technique, and 3) a non-thrust lumbar mobilization technique. A variety of clinicians in geographically diverse practice settings will be used to permit comparison of outcomes within different practice settings.

## Methods

The Institutional Review Boards at Concord Hospital, Concord, New Hampshire and at Intermountain Healthcare Urban Central Region, Salt Lake City Utah have granted approval for the study.

### Study sample

Two hundred forty subjects with LBP will be recruited from physical therapy clinics in four different geographical locations (60 subjects per location). These sites will provide a diversity of geographic and practice settings. A flow chart demonstrating patient recruitment, study design and timing of data collection can be seen in Figure 1.

The study will include patients who meet the following inclusion criteria:

**1**. Chief complaint of pain and/or numbness in the lumbar spine, buttock, and/or lower extremity

**2**. Oswestry disability score (OSW) of at least 25%

**3**. Age greater than 18 years and less than 60 years

**4**. At least four out of five of the following criteria:

**a**. Duration of current episode < 16 days (judged from the patient's self-report)

**b**. No symptoms extending distal to the knee (judged from the pain diagram)

**c**. Fear-Avoidance Beliefs Questionnaire work subscale (FABQ-W) score <19

**d**. At least one hip with >35° internal rotation range of motion (measured in prone)

**e**. Stiffness in the lumbar spine (judged from segmental mobility testing)

The following exclusion criteria will be used for this study:

**1**. Red flags noted in the participant's general medical screening questionnaire (i.e. tumor, metabolic diseases, RA, osteoporosis, prolonged history of steroid use, etc.)

**2**. Signs consistent with nerve root compression, this includes *any one*of the following:

**a**. Reproduction of low back or leg pain with straight leg raise at less than 45°

**b**. Muscle weakness involving a major muscle group of the lower extremity

**c**. Diminished lower extremity muscle stretch reflex (Quadriceps or Achilles tendon)

**d**. Diminished or absent sensation to pinprick in any lower extremity dermatome

**3**. Prior surgery to the lumbar spine or buttock

**4**. Current pregnancy

**5**. Past medical history of osteoporosis or spinal compression fracture

**6**. Inability to comply with treatment schedule (weekly sessions for four weeks)

#### Examination procedures

All patients meeting the inclusion/exclusion criteria will be eligible for participation. Patients who agree to participate will sign an informed consent document approved by the Institutional Review Board at the respective study site. A therapist blind to group assignment will perform all evaluation procedures. After obtaining informed consent, all subjects will then complete the remainder of the self-report questionnaires and a physical examination. The following self-report questionnaires will be completed by the patient at the baseline examination, demographic data, Numeric Pain Rating Scale (NPRS) [24], Pain Diagram [25], Oswestry Disability Questionnaire (OSW) [26], Fear-Avoidance Beliefs Questionnaire Work (FABQ) [19], Patient Global Rating of Change (GROC) [27]. Following completion of self-report measures the patient will undergo a standardized historical and physical examination. The questionnaires and the physical examination will be repeated following completion of the four-week treatment program. The OSW, NPRS, and GROC will also be completed after the first week (2 sessions) of treatment and at a 6-month follow-up.

#### Randomization

A random number generator will be used to establish randomization lists prior to the initiation of the study. An individual not involved with data collection will generate separate randomization lists for each participating site. Once the baseline examination is completed, a second therapist blind to the baseline examination will open the randomization envelope indicating the patient's treatment group assignment that corresponds to the patient's unique identification number. Patients will receive treatment according to their group assignment for 2 sessions within the first week. Following this all subjects will continue with physical therapy treatment for 3 additional visits (once weekly for 3 weeks) with a standardized exercise regimen.

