### Data analysis

We will recruit 60 patients per clinical site, for a total enrollment of 240 patients across the four geographical locations. A sample size of 240 patients will provide 93% power to detect a minimal difference of 5 points on the OSW assuming a common standard deviation of 10 points. A sample size of 60 within each geographical location will provide 83% power to detect a difference of 9 points on the OSW assuming a standard deviation of 10 points. This sample size will provide sufficient power to detect a minimum clinically important difference in the entire sample, and a moderate difference within a geographical location.

Descriptive statistics, including frequency counts for categorical variables and measures of central tendency and dispersion for continuous variables will be calculated to summarize the data. Baseline demographic data will be compared across treatment groups to assess the adequacy of the randomization. If appropriate, statistical adjustments will be made for baseline characteristics that are significantly different between groups. An intention-to-treat analysis will be utilized in which all participants will be analyzed in the group to which they were originally assigned. All drop-outs and the reason for dropping out of the study will be reported. An *a priori *alpha level of 0.05 will be used for all analyses. All data will be screened to ensure they meet the assumptions for the inferential statistical analyses described below. If they do not meet the necessary assumptions, appropriate non-parametric procedures will be utilized.

The primary aim will be tested with analysis of variance (ANOVA) using the change in OSW score from baseline to 4-weeks (OSW_Baseline _– OSW_4-weeks_) as the dependent variable. The independent variable will be treatment with three levels (lumbo-pelvic manipulation, alternative lumbar manipulation, lumbar mobilization). A second ANOVA will be conducted on the one-week OSW change scores to test for the presence of an immediate treatment effect. We will also repeat the ANOVA procedure for the 6-month follow up outcomes, and using pain rating as the dependent variable.

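### Allocation is listed by site, but the primary ANOVA and its repeats have treatment as the only factor, so any site difference in OSW change stays in the error term and costs some precision

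*Protocol article*

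**What the plan says.** Allocation is organised by site. Under Randomization: "An individual not involved with data collection will generate separate randomization lists for each participating site". No block size or other balancing device is given.

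The sites are meant to differ. Under Study sample: "These sites will provide a diversity of geographic and practice settings", with 60 patients planned at each of four locations. The Background section on generalizability also wants outcomes compared within practice settings.

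The primary model is stated explicitly under Data analysis: "The primary aim will be tested with analysis of variance (ANOVA) using the change in OSW score from baseline to 4-weeks", followed by "The independent variable will be treatment with three levels (lumbo-pelvic manipulation, alternative lumbar manipulation, lumbar mobilization". The Abstract says the same. The 1-week, 6-month and pain analyses repeat this ANOVA. Site appears in none of these models.

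The one route to adjustment is conditional: "If appropriate, statistical adjustments will be made for baseline characteristics that are significantly different between groups". Site is not named there.

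**The concern.** The design treats site as a factor worth controlling at allocation, and the sites were picked to be unlike one another. If mean improvement in OSW differs between them, a treatment-only ANOVA counts that difference as unexplained variation. The residual mean square is larger than it need be, and the comparison of three active techniques is less sharp. Precision matters here because the Background considers it plausible that different techniques give similar outcomes, and a null result is easier to interpret with narrower intervals.

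The conditional adjustment clause does not repair this. If the lists balance the arms within site, a test for a difference between groups will not pick site up. If they do not, it would be triggered only by a chance imbalance. In either case the case for including site rests on its relation to outcome, which that clause does not examine.

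**Working it through.** **Inputs from the article.** N = 240; four sites of 60; three arms; difference 5 points; SD 10; alpha 0.05; stated power 93%. For one site: n = 60, difference 9 points, stated power 83%.

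**Assumptions.** Equal arms (80 per arm, 20 per arm per site). R is the share of the variance of OSW change explained by site. The article gives no value, so R = 5%, 10% and 15% are used. SD 10 is read as the total SD unless stated otherwise.

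**1. Reproduce the plan's figures.** For a three-arm F test with one arm differing by d from the other two, the noncentrality is λ = N × (2/9) × (d/SD)².

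- N = 240, d = 5: λ = 240 × (2/9) × 0.25 = 13.33, error df 237, power 91.2% (stated 93%).
- n = 60, d = 9: λ = 60 × (2/9) × 0.81 = 10.8, error df 57, power 82.5% (stated 83%).

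Both are within 2 points. With the middle arm halfway, power is 81.0% and 69.9%, which fits neither figure. The one-arm-differs pattern is therefore the reference.

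**2. Add site.** The residual variance becomes 100 × (1 − R), λ becomes 13.33/(1 − R), and the error df become 237 − 3 = 234. The SE of a pairwise difference is 10 × √((1 − R) × 2/80).

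| R | SE | λ | Power with site |
|---|---|---|---|
| 0 | 1.58 | 13.33 | 91.2% |
| 5% | 1.54 | 14.04 | 92.5% |
| 10% | 1.50 | 14.81 | 93.8% |
| 15% | 1.46 | 15.69 | 95.1% |

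The R = 0 row shows that three spent degrees of freedom have no visible cost.

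**3. Level of the treatment-only test when arms are balanced within site.** Site differences then cancel from the arm means but remain in the residual. Under the null the numerator mean square has expectation 100 × (1 − R), while the denominator is close to 100. The F ratio is shrunk by about (1 − R), and its level is roughly exp(−3.034/(1 − R)), where 3.034 is the 5% critical value on 2 and 237 df:

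- R = 5%: exp(−3.194) = 4.1%
- R = 10%: exp(−3.371) = 3.4%
- R = 15%: exp(−3.569) = 2.8%

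This shortcut runs slightly low, since at R = 0 it gives exp(−3.034) = 4.8% rather than 5%. Integrating over the exact distribution of the denominator (noncentral chi-square, 237 df, noncentrality 240R/(1 − R)) gives 4.3%, 3.6% and 2.9%. Simulations of the balanced case gave 4.2% to 4.7% at R = 5%, 3.5% to 3.7% at 10% and 2.9% at 15%. With site in the model the level stays at about 5%.

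**4. Level under simple randomisation within each site.** In 20,000 simulated trials per setting, the treatment-only test rejected a true null 4.9%, 5.1% and 5.0% of the time at R = 5%, 10% and 15%. The test is then valid.

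**5. Gain in power, treatment-only against site-adjusted, one arm 5 points better.** Each cell of the simulation used 20,000 trials.

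| R | Balanced within site | Simple randomisation per site |
|---|---|---|
| 5% | 91.8% to 92.7% | 90.9% to 91.8% |
| 10% | 91.8% to 93.9% | 91.2% to 93.3% |
| 15% | 92.7% to 95.1% | 90.9% to 94.4% |

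The gain is about 1 to 3.5 points across both schemes.

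**6. If SD 10 is a within-site SD.** The article does not say which it is. On this reading the total SD is 10/√(1 − R), and treatment-only power falls to 89.6%, 87.9% and 85.9% at R = 5%, 10% and 15%, against about 91.2% with site in the model.

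**The case against.** The strongest reply is that this is a small efficiency point. The outcome is a change score, so site differences in baseline level are already subtracted and only differences in improvement remain. Eligibility and treatment are common to all sites. A site share near zero is as compatible with the article as 15%. All of this stands, and it is why the effect is shown as a range that starts at no gain.

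Several stronger readings are tempting, and the article does not support them.

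- A reader might infer that the reported SE and p-value must be too large. That requires balance within site. Separate lists alone do not ensure it, and no blocking is stated. With simple lists the test keeps its level.
- A reader might infer that leaving site out lets it confound the arm means. Random allocation within site rules out systematic bias. Chance imbalance adds noise, which the treatment-only SE already reflects on average.
- A reader might put the gain at 81% rising to 87%. Those figures belong to a middle-arm-halfway pattern, which the article does not state and which does not match its power figures.
- A reader might say that site is disregarded altogether. The article sizes each location at 60 with its own power statement and intends comparison within settings. What is absent is a site term in the models it describes.

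It can also be said that a condensed article leaves covariates to the analysis plan. That would answer a complaint about silence. Here the article names the dependent variable and the independent variable of the primary test, so the point concerns what is fixed.

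**Conclusion.** The point holds as a modest loss of precision. The trial randomises by site and then analyses without it. If site is related to OSW change, the treatment-only ANOVA gives up about 1 to 3.5 points of power for a 5-point difference when site explains 5% to 15% of the variance. If allocation is balanced within site, it also runs below its nominal 5% level. Any error is in the conservative direction or absent: there is no inflation of type I error and no systematic bias.

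The size rests on an assumed site share, on equal arms, on one arm differing from the other two, and on SD 10 being a total SD. If it is a within-site SD, the shortfall is somewhat larger. The change is worth making because it is nearly free, but the trial's validity does not depend on it.

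**What to change.** In Data analysis, add site (four levels) as a fixed factor alongside treatment in the primary ANOVA, and carry it into the 1-week, 6-month and pain repeats. State this before outcome data are seen, and not through the clause on significant baseline differences. It would help to say whether the per-site lists are blocked and whether the SD of 10 is within-site or total, since both determine how much the change matters.

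The cost is one phrase in the text and 3 of the 237 error degrees of freedom. The sample size does not change.

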#### Blinding

Due to the nature of this study, it is not possible to blind the patient or the treating therapist to the treatment received. We will blind the examining therapist performing the baseline and outcome assessments. The examining and treating therapists will be different individuals and the examining therapist will remain blind to the patient's treatment group assignment at all times. Patients will be instructed not to discuss the particular manual therapy technique received with the examining therapist.

